## **PART II: STUDY PROTOCOL**

### **5. TRIAL OBJECTIVES**

To assess the safety and efficacy of sorafenib in combination with vinorelbine, as first line treatment for metastatic breast cancer.

#### **5.1 Primary Objectives**

**Phase I:** To assess the optimal dose of sorafenib in combination with vinorelbine.  
**Phase II:** To assess the clinical benefit (response rate + disease control rate) in women with metastatic breast cancer, when treated with this combination at the optimal doses.

#### **5.2 Secondary Objectives**

To assess:

- toxicity and safety;
- median time to best response;
- median duration of response;
- median progression free survival;
- overall 2 year survival in women with metastatic breast cancer, when treated with

the combination of vinorelbine and sorafenib at optimal doses.

To assess pharmacokinetic steady state parameters and interaction between vinorelbine and sorafenib when administered together at optimal doses.

## 6. STUDY DESIGN

This will be a non-randomized, open label, phase I/II, multi-centre study of sorafenib in combination with fixed doses of vinorelbine as first-line treatment for women with metastatic breast cancer.

In the Phase I of the study, 6-12 patients will be recruited in a single center (Jewish General Hospital, Montreal).

In the Phase II part, 21-24 more patients will be recruited and treated in six different centers in Quebec.

The first part of the study will test increasing doses of sorafenib, combined with regular administration of vinorelbine at fixed therapeutic doses (30 mg per square meter on days 1 and 8 of 21-day cycles).

Dose escalations will be made in subsequent cohorts of patients, up to the recommended dose for sorafenib monotherapy. Sorafenib doses will be: 200 mg bid (cohort I) and 400 mg bid (cohort 2).

In the second part of the trial, the cohort of patients treated at the recommended dose will be expanded, up to a total of 27 patients treated with this schedule of the combination regimen (see Section 16.2).

Six patients treated at the recommended dose will be assessed for pharmacokinetic analysis.

Clinical follow-up, including physical examination, laboratory testing and evaluation of adverse event will be performed on day 1 and 8 of each cycle.

Patients will have appropriate radiological imaging to document baseline disease within 4 weeks prior to study entry. Radiological imaging will be repeated regularly after every two cycles, until disease progression or unacceptable toxicity, up to 8 cycles (or after at least 4 cycles after achievement of the best response obtained).

Those patients whose disease has not progressed during the combination treatment, will continue receiving sorafenib alone at the dose of 400 mg bid and will be monitored every 42 days, with clinical and radiological follow-up.

All patients will be followed for a minimum of 2 years for survival and residual toxicity.

Safety will be assessed by examination of adverse events, clinical laboratory data, and vital signs. Adverse events, use of growth factors, and changes in laboratory parameters will be summarized and tabulated. Objective response (CR, PR, SD, and PD) will be summarized and tabulated. Time to response, duration of response, time to progression, and survival will be calculated. Kaplan-Meier estimates and curves will be used to present these time-to-event data.

## 6.1 Enrollment Procedures

Registration will be performed after all pretreatment procedures have been completed (section 11.1) and the investigator has reviewed all inclusion and exclusion criteria (sections 8 and 9).

Registration and assignment of subject number will be accomplished by facsimile. Subject number assignment will begin in ascending order starting and will be site-specific (i.e. site 1 gets patient numbers 10-19, site 2 gets patient numbers 20-29, etc.).

## 7. INCLUSION CRITERIA

Patients meeting the following criteria will be eligible for enrollment:

1. Women affected by histologically proven metastatic breast cancer.
2. Tumor not susceptible to therapy with trastuzumab, defined as FISH negative for HER-2 amplification or immunohistochemistry 0-1+ for HER-2 expression.
3. Female, age  $\geq 18$ .
4. Documented measurable disease by appropriate radiologic imaging according to RECIST criteria (see Appendix E). Lesions in previously irradiated areas are not considered measurable disease, unless progression has been documented post-radiation.
5. ECOG performance status 0-1 (see Appendix B).
6. Life expectancy  $> 6$  months.
7. Adequate bone marrow function, as indicated by:
  - hemoglobin  $\geq 90$  g/L;
  - neutrophils  $\geq 1.5 \times 10^9/L$ ;
  - platelets  $\geq 100 \times 10^9/L$ .
8. Adequate renal function, as indicated by serum creatinine  $\leq 1.5$  times the upper limit of normal and/or Creatinine Clearance calculated as  $>50\%$  lower normal limit, or estimated as  $\geq 50$  ml/min (Appendix C).
9. Adequate liver function, as indicated by:

- bilirubin  $\leq 1.5$  times upper normal limit;
- AST and ALT  $\leq 2$  times upper normal limit.
- 10. Left ventricular ejection fraction (LVEF)  $\geq 50\%$  as measured by either multigated acquisition (MUGA) scan or echocardiogram (ECHO).
- 11. No therapy for breast cancer in the 4 weeks preceding the therapy start.
- 12. Women of childbearing potential must be using adequate contraception and have a negative pregnancy test at the time of enrollment.
- 13. Patient able to understand and give written informed consent.

## 8. EXCLUSION CRITERIA

Patients are excluded from the study if any of the following criteria is met:

1. Patients with locally advanced breast cancer or stage IIIb only.
2. Presence of only non-measurable disease.
3. Previous (neo)adjuvant chemotherapy with vinorelbine.
4. Any previous anti-angiogenic therapy.
5. Any previous chemotherapy for metastatic breast cancer. Previous hormonal treatments or radiotherapy for metastatic disease are allowed.
6. Radiotherapy, chemotherapy or hormonal therapy for breast cancer in the last 4 weeks prior to starting the study treatment.
7. Major surgery within 4 weeks of first study treatment, or minor surgery (including placement of an access device) within 7 days of therapy start.
8. Presence of life-threatening disease or central nervous system localizations.
9. Evidence of HER-2 positive breast cancer, defined as FISH-positive for amplification or score 3+ by immunohistochemistry.
10. Any other possibly active primary tumor, except basal cell carcinoma of the skin, or carcinoma in situ of the cervix.
11. Clinically significant hepatic disease with respect to hepatitis B, hepatitis C, cirrhosis or other liver diseases.
12. Uncontrolled bacterial, viral or fungal infection.
13. Previous history of ischemic disease.
14. Patients with previous history of thrombo-embolic events, or with documented risk factors for thrombotic disease other than cancer.
15. History of gross hemorrhage within the past 6 months (e.g., hemoptysis or hematuria requiring medical intervention).
16. Uncontrolled hypertension.
17. Other serious medical conditions, such as uncontrolled cardiac disease, severe pulmonary disease, uncontrolled diabetes.
18. Patient exhibiting confusion or disorientation.
19. Any condition (medical, psychological, geographical) that would prevent adequate follow-up.
20. Patient is pregnant, or is breast-feeding, or is unwilling to use adequate contraception.
21. Failure to give informed consent.

## 9. THERAPY ADMINISTRATION

### 9.1 Phase I

In the first part of the study patients will test increasing doses of sorafenib, combined with a fixed schedule of vinorelbine.

Vinorelbine will be administered at the dose of 30 mg per square meter on days 1 and 8 of 21-day cycles.

Dose escalations will be made only for sorafenib, in subsequent cohorts of patients, up to the recommended dose for sorafenib monotherapy.

Planned dose levels for sorafenib are: 200 mg bid (cohort 1) and 400 mg bid (cohort 2).

Three patients will be enrolled at the first dose level. In the absence of a dose-limiting toxicity at the end of the first cycle, three patients will be enrolled in the second dose level. If any patient experiences a dose-limiting toxicity, up to three additional patients will be enrolled at the same dose level.

Only in case of dose-limiting toxicity observed in two or more patients in the first cohort, further recruitment will be at the dose of 200 mg qd for sorafenib (cohort –1).

The maximum tolerated dose will be defined when two or more patients in a cohort of six patients experience a dose-limiting toxicity. The recommended dose (RD) for the second part of the study will be the dose level immediately preceding, or, in the absence of a documented maximum tolerated dose, the dose of 400 mg bid.

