## 12. DEFINITION OF DOSE-LIMITING TOXICITY (DLT)

Dose-limiting toxicity is defined as one or more of the following:

- 1) Febrile neutropenia, defined as a temperature  $\geq 38.5^{\circ}\text{C}$  in the presence of ANC  $< 1.0 \times 10^9/\text{L}$ .
- 2) Grade 4 neutropenia lasting more than 5 days.
- 3) Grade 4 thrombocytopenia ( $< 25 \times 10^9/\text{L}$ ) or anemia ( $< 65 \text{ g/L}$ ).
- 4) Grade 3 thrombocytopenia ( $< 50 \times 10^9/\text{L}$ ), if lasting more than 5 days.
- 5) Grade 3 AST-ALT increase ( $> 5.0 \times \text{ULN}$ ), if lasting more than 5 days.
- 6) Grade 3 rash, if lasting more than 5 days after suspension of sorafenib.
- 7) Grade 3 diarrhea, if lasting more than 24 hours from suspension of sorafenib and adequate treatment with loperamide or diphenoxylate/atropine.
- 8) Other non-hematological toxicity of Grade  $\geq 3$ , except unpremedicated nausea or vomiting, vinorelbine-induced peripheral phlebitis or extravasation ulceration.
- 9) Impossibility to start the second cycle of therapy within 14 days from the planned day, as a consequence of toxicity.

Any patient experiencing a DLT at any cycle will be evaluated by the investigator, who will assess the utility for the patient of continuing the study treatment at lower doses, rather than definitively terminating his participation to this trial.

No patient experiencing a DLT will be retreated at the same dose. The investigator will evaluate risks and benefits for the patient, being aware of the multiple therapeutic possibilities that are usually available for patients at this stage of disease.

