### 14. DISCONTINUATION OF THERAPY AND WITHDRAWAL FROM STUDY

A patient will stop receiving the study treatment and will be withdrawn from the study when any of the criteria is met:

- Progression of disease based on physical examination or radiological

- Patient's inability to tolerate therapy despite dose reduction. This includes allergic reactions not controlled with slower infusions and routine pre-medications.
  - Patient experiencing an adverse event that would mandate a dose reduction below 200 mg qd for sorafenib, or below 20 mg/m^2 for vinorelbine.
  - Withdrawal of informed consent.
  - Patient evaluated as non-compliant by the investigator.
  - Need of new anticancer treatments. Patient requiring palliative radiation therapy should have study drugs withheld during the course of radiation therapy and until recovery (at least 15 days after radiation). Such patients may be retreated with study drugs, provided that the metastases do not represent progression of disease and there is no evidence of radiation recall reaction.
  - Patient with clinical signs or laboratory test results consistent with pregnancy. The pregnancy will be followed up via the Pregnancy Monitoring Form.
- The investigator can discontinue the patient at any time, at his/her discretion.

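### Section 9.1 ties the MTD to a six-patient cohort and gives no two-DLT stop at 400 mg bid, so two or three DLTs in the first three patients there lead either to pointless further exposure or, read literally, to 400 mg bid as the recommended dose

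*Protocol*

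**What the plan says.** Protocol Section 9.1 plans two sorafenib levels with fixed vinorelbine, 200 mg bid and then 400 mg bid, with 200 mg qd as a fallback. Its rules are:

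- **Escalation:** "In the absence of a dose-limiting toxicity at the end of the first cycle, three patients will be enrolled in the second dose level".
- **Expansion:** "If any patient experiences a dose-limiting toxicity, up to three additional patients will be enrolled at the same dose level". One, two or three DLTs among the first three patients are not distinguished.
- **Step-down:** the only two-DLT instruction concerns the first level: "dose-limiting toxicity observed in two or more patients in the first cohort, further recruitment will be at the dose of 200 mg qd".
- **MTD:** "The maximum tolerated dose will be defined when two or more patients in a cohort of six patients experience a dose-limiting toxicity".
- **Recommended dose:** the level below the MTD or, "in the absence of a documented maximum tolerated dose, the dose of 400 mg bid".

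Section 14 withdraws any "Patient experiencing an adverse event that would mandate a dose reduction below 200 mg qd for sorafenib", so 200 mg qd is the lowest dose allowed. Section 6 puts Phase I at 6 to 12 patients in one centre. Section 4 reports no previous human experience with this combination.

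**The concern.** The MTD definition assumes six patients at the level, while the expansion rule sets only an upper limit on the patients added. The two agree when one of the first three has a DLT. They do not agree when two or three do, and at 400 mg bid no other sentence settles the matter. The site then either treats more patients at a dose that already has the number of DLTs that defines the MTD, or stops and has no documented MTD. In the second case the default clause names 400 mg bid.

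The recommended dose is the one carried into the Phase II expansion, to a total of 27 patients. A dose-finding rule for an untested combination should not give the right answer only when the team sets its wording aside.

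**Working it through.** **1. The plan's own figure.** With three or six patients at each of two levels, the smallest Phase I is 3 + 3 = 6 and the largest is 6 + 6 = 12. This reproduces the range in Section 6 and shows that six is the ceiling per level.

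**2. Outcomes at 400 mg bid under the letter of Section 9.1.**

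| DLTs in first three | Cohort filled to six? | Literal MTD definition met? | Recommended dose as written |
|---|---|---|---|
| 0 | No | No | 400 mg bid |
| 1, none in the next three | Yes | No | 400 mg bid |
| 1, at least one in the next three | Yes | Yes | 200 mg bid |
| 2 or 3 | Yes | Yes, always | 200 mg bid |
| 2 or 3 | No | No | 400 mg bid |

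The last two rows are the problem. The same observed toxicity gives opposite written doses, depending only on whether more patients are added.

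**3. Why the added patients cannot matter.** Let d be the DLTs in the first three patients and y those in the next three. If d is at least 2, then d + y is at least 2 for every y from 0 to 3. The decision is fixed before the fourth patient is enrolled.

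**4. How often this state is reached.** The protocol gives no DLT rate for the combination, so p = 0.20, 0.33 and 0.50 are assumptions. Given that 400 mg bid has opened, P(two or more DLTs in three) = 3p²(1 − p) + p³:

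- p = 0.20: 3 × 0.04 × 0.80 + 0.008 = 0.104
- p = 0.33: 3 × 0.1089 × 0.67 + 0.0359 = 0.255
- p = 0.50: 3 × 0.25 × 0.50 + 0.125 = 0.500

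**5. Cost of filling the cohort.** Expected DLTs in three further patients = 3p = 0.60, 0.99 and 1.50.

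**6. The lowest level.** If 200 mg qd has two or more DLTs, the rule points to the level below it. None exists, and no outcome is stated.

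**The case against.** The strongest reply is that six is naturally read as a cap and two DLTs as the threshold, so two of three already meets it. The first-level step-down, which does not mention six, supports this reading. That step-down may be confined to the first level only because it opens an unplanned dose; at 400 mg bid a lower level already exists. The expansion rule also sets a maximum, so the site may add nobody. Two or more DLTs at 200 mg qd would in practice leave no dose to expand.

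Much of this stands. Section 9.1 does not oblige the site to enrol three more patients, and a sensible team would go to 200 mg bid. But adding nobody is exactly the branch in which the literal definition is unmet and the written default is 400 mg bid. The sensible answer has to be supplied from outside the text.

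Three stronger readings are tempting, and the document does not support them:

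- **A conflict with Section 12.** A reader might set the expansion rule against "No patient experiencing a DLT will be retreated at the same dose". That sentence governs retreatment of the same patient. Enrolling new patients at a level where one DLT occurred is how this kind of expansion works.
- **A wider count.** A reader might add the cohorts with one DLT in three and a second at patient 4 or 5. Those cohorts were properly expanded, at most two places remain, and they may already be filled.
- **Premature escalation.** A reader might infer that deciding at the end of cycle 1 misses the DLT criterion "Impossibility to start the second cycle of therapy within 14 days from the planned day, as a consequence of toxicity", which can stay open until day 22 + 14 = 36. For blood counts this is speculative. Section 2.2 gives neutropenia lasting 7 to 14 days. With an assumed onset on day 8 to 15 it ends between day 8 + 7 = 15 and day 15 + 14 = 29, which is 7 days inside the limit. The restart thresholds in Section 11.1 (neutrophils 1.0 and platelets 75 × 10⁹/L) are lenient. Waiting for this criterion is at most an optional clarification.

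**Conclusion.** The point holds as a defect in the written dose-finding rule. After two or three DLTs in the first three patients at 400 mg bid, Section 9.1 either permits three more exposures that cannot change the recommended dose or, read literally, recommends the dose that just failed. Nothing elsewhere in the protocol repairs this.

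At assumed DLT rates of 20%, 33% and 50%, the state arises in about 10%, 25% and 50% of cohorts opened at 400 mg bid, and filling the cohort brings 0.6, 1.0 and 1.5 expected further DLTs. These percentages are chances of reaching the unclear state. They are not chances that the trial picks a wrong dose, which a reader might infer but which would require a team to follow the letter against its own judgement. The gap in the wording does not depend on the assumed rates; only its size does.

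**What to change.** Reword Section 9.1 so that, at any dose level:

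- the MTD is defined by two or more DLTs in up to six patients;
- enrolment at that level stops once the second DLT occurs;
- the recommended dose is then the next lower level;
- two or more DLTs at 200 mg qd means that there is no recommended dose and Phase II does not open.

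The 400 mg bid default then applies only when that level has been tested with fewer than two DLTs. As an option, a sentence could ask the site to hold escalation while a first-level patient's second cycle is delayed for toxicity.

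The cost is protocol wording. The ceiling of 12 Phase I patients and the Phase II size do not change. The price is less DLT information at a level already judged too toxic. The optional sentence would delay escalation by at most 36 − 21 = 15 days, and only when a second cycle is late.

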## 10.2 Monitoring of patients treated with combination therapy

During administration of sorafenib and vinorelbine, in both study phases, patients will be routinely assessed for adverse events and cell blood count on days 1 and 8 of every cycle.

A complete biochemical blood analysis will be routinely performed at day 1 of each cycle.

Blood samples will be collected on the same day of therapy administration, or, in case of necessity, within the preceding 24 hours.

Physical examination, laboratory testing and evaluation of adverse event will be performed more often, if clinically indicated.

Only for patients treated during the phase I (dose escalation) part of the study, additional blood samples will be collected for cell blood count on day 15 of the first two cycles and for hepatic function markers on day 8 and 15 of the first two cycles. The utility of maintaining these additional tests for patients treated in the phase II cohort will be discussed by the investigators after completion of the phase I.

Radiological imaging will be repeated regularly every 6 weeks (two cycles), unless all measurable disease is assessable by physical exam.

Assessment of tumor response will be performed as long as the patient remains on study, or until disease progression for patients removed from the study for other reasons. Patients who achieve complete or partial response will be re-evaluated at least 4 weeks later to confirm the initial observation of response.

A cardiac re-evaluation through 12-lead EKG plus echocardiogram or MUGA scan will be repeated every 12 weeks (4 cycles), or more often if clinically indicated.

Patients receiving sorafenib monotherapy, after documented disease control, will be assessed for adverse events, cell blood count and biochemical blood analysis on day 1 of 21-day cycles for the first 8 cycles of sorafenib monotherapy, and every 2 cycles (42 days) thereafter, until patient's removal from the study. Physical examination, laboratory testing and evaluation of adverse events will be performed more often, if clinically indicated.

Chest X-ray, bone scan, abdomen ultrasound will be repeated if clinically indicated or, for patients in study more than 12 months, approximately once a year.

All patients will be followed for a minimum of two years for survival.

schematic layout of procedures planned for regular assessment of patients on study.

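### The MTD is judged on six patients, but the recommended dose can be settled on three, and nothing says that DLTs in the next patients at that level can change it

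*Protocol*

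**What the plan says.** Protocol section 9.1 sets out the escalation.

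- Start: "Three patients will be enrolled at the first dose level".
- Escalation: "In the absence of a dose-limiting toxicity at the end of the first cycle, three patients will be enrolled in the second dose level".
- Enlargement: "If any patient experiences a dose-limiting toxicity, up to three additional patients will be enrolled at the same dose level".
- MTD: "The maximum tolerated dose will be defined when two or more patients in a cohort of six patients experience a dose-limiting toxicity".
- RD when an MTD is found: "The recommended dose (RD) for the second part of the study will be the dose level immediately preceding".
- RD otherwise: "in the absence of a documented maximum tolerated dose, the dose of 400 mg bid".

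Neither RD sentence gives a number of patients who must have been treated at that level.

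Section 6 puts Phase I at 6-12 patients in one centre and continues: "In the Phase II part, 21-24 more patients will be recruited and treated in six different centers in Quebec". Sections 6 and 9.2 fix the total at the RD at 27, counting the Phase I patients treated there.

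Section 10.2 limits the day-15 blood counts and the day-8 and day-15 hepatic markers of the first two cycles to Phase I patients. For Phase II it says: "The utility of maintaining these additional tests for patients treated in the phase II cohort will be discussed by the investigators". Footnote 7 of the assessment schedule allows these tests at the RD if they are thought necessary.

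Sections 11.9 and 12 say what happens to an individual patient after a DLT. Section 16 contains no toxicity rule for the Phase II cohort.

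**The concern.** Dose selection is the primary objective of Phase I. The two sentences that decide it rest on different amounts of evidence: six patients to call a level too toxic, possibly three to adopt it. There are two routes to an RD based on three patients:

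1. 400 mg bid shows no DLT in three patients, so no MTD is documented.
2. 400 mg bid meets the MTD criterion, and 200 mg bid had been left after no DLT in three.

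Patients 4 to 6 at that level are then ordinary Phase II patients. If two or more of them have a DLT, the level has met the protocol's own two-in-six criterion. No section says that this reopens the RD, and as written it stays the RD for up to 27 − 6 = 21 more patients.

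Section 4 says that the combination has not yet been given to humans, and section 17 starts the pharmacokinetic interaction work only once the RD is defined. Several DLTs in section 12 depend on an abnormality lasting more than five days. By default, the extra laboratory tests that would help to document such durations stop with Phase I.

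**Working it through.** **Step 1. The protocol's own range.** The total at the RD is 27 (sections 6 and 9.2). A level holds three patients if no DLT occurs, and up to six otherwise (section 9.1).

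- 27 − 3 = 24 and 27 − 6 = 21, which reproduces 21-24 in section 6.
- The lower end of 6-12 in Phase I is 3 + 3, and the upper end is 6 + 6.

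An RD resting on three patients is therefore within the plan.

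**Step 2. Chance that a level is accepted.** Let p be the true DLT rate and q = 1 − p. The protocol states no target rate, so 33%, 40% and 50% are assumptions.

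- Current rule (0/3, or 1/3 followed by 0/3): A = q³ + 3pq² × q³
- The two-in-six criterion always read on six patients (at most 1/6): B = q⁶ + 6pq⁵

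| p | A | B |
|---|---|---|
| 0.33 | 0.3008 + 0.4444 × 0.3008 = 0.434 | 0.0905 + 0.2673 = 0.358 |
| 0.40 | 0.2160 + 0.4320 × 0.2160 = 0.309 | 0.0467 + 0.1866 = 0.233 |
| 0.50 | 0.1250 + 0.3750 × 0.1250 = 0.172 | 0.0156 + 0.0938 = 0.109 |

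At p = 0.10, acceptance moves only from 90.6% to 88.6%.

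**Step 3. How often the decision differs.** A − B is the chance of no DLT in the first three patients followed by two or more in the next three: q³ × (3p²q + p³).

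- p = 0.10: 0.729 × 0.028 = 0.020
- p = 0.20: 0.512 × 0.104 = 0.053
- p = 0.33: 0.3008 × 0.2548 = 0.077
- p = 0.40: 0.216 × 0.352 = 0.076
- p = 0.50: 0.125 × 0.500 = 0.062

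**Step 4. How often an accepted level rests on three patients.** This is q³ / A: 0.3008/0.434 = 69% at p = 0.33, 0.216/0.309 = 70% at 0.40 and 0.125/0.172 = 73% at 0.50.

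**Step 5. Precision.** The exact one-sided 95% upper limit for the DLT rate is:

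- 0/3: 1 − 0.05^(1/3) = 63%
- 0/6: 1 − 0.05^(1/6) = 39%
- 1/6: the p that solves q⁶ + 6pq⁵ = 0.05, which is 58%

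**Step 6. Patient numbers if 400 mg bid had 0/3 and were then read on six.**

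- It passes: 3 at 200 mg bid and 6 + 21 = 27 at 400 mg bid, 30 in all. The current plan gives 3 + (3 + 24) = 30.
- It fails: 6 at 400 mg bid and 27 at 200 mg bid (including the first three there), 33 in all. That is three more than 30.

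**The case against.** The best defence is that the plan is deliberate and internally consistent. Enlarging a cohort only after a DLT is a familiar sequential scheme, and the ranges in section 6 fit it exactly. Only two levels are planned, and escalation stops at the dose recommended for sorafenib monotherapy. This stands: a reader might infer an arithmetical contradiction between sections 6 and 9.1, and there is none. What differs is the number of patients behind the MTD sentence and behind the RD sentence.

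The gain is also modest. The decision changes in at most about 8% of cases over the assumed rates, and a level with a 33% DLT rate would still pass 36% of the time on six patients. Comparing 0/3 with 0/6 alone flatters the six-patient reading, because 1/6 also passes and its upper limit is 58%, close to the 63% after 0/3. This too stands.

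Three stronger readings are tempting, but the protocol does not support them.

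- *DLTs in Phase II have no consequence.* Section 11.9 makes a sorafenib reduction mandatory after a DLT, section 12 bars retreatment at the same dose at any cycle, and section 15.5 requires rapid reporting of serious events. Only a consequence for the RD is missing.
- *Monitoring is certain to be lighter.* That is the written default. Section 10.2 and schedule footnote 7 let the extra tests be kept.
- *Six-patient evidence never costs a patient.* That is true only if the level passes (step 6).

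**Conclusion.** The point holds as a weakness in how section 9.1 fixes the RD. A level can be adopted on 0/3, and nothing in the protocol lets DLTs in the next patients at that level alter the choice, even if they bring it to two in six. At assumed DLT rates of 33%, 40% and 50%, the chance of acceptance is 43%, 31% and 17%, against 36%, 23% and 11% on six patients. That is a difference of 6 to 8 percentage points, with almost no loss at a 10% rate. The figures assume independent patients with a common DLT rate, full ascertainment of DLTs, and rates that the protocol does not supply.

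A reader might infer that a level failing the two-in-six criterion will become the RD. The protocol shows only that it could. The change is still worth making, because it concerns the Phase I primary objective and costs little.

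**What to change.** The sponsor should reconcile the MTD and RD sentences of section 9.1 so that both rest on the same number of patients, and should state what DLTs in the next patients at the RD do to the RD. Which number and which consequence to adopt is for the sponsor to decide.

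These passages should be aligned with that decision:

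- Section 6: the 6-12 and 21-24 ranges. If six patients at the RD were required and counted in Phase I, the two-level paths would give 9-12 and 21.
- Section 10.2 and schedule footnote 7: whether the additional tests apply to patients whose DLTs still bear on the RD.
- Section 17: whether the six pharmacokinetic patients, who start sorafenib on day 4 of cycle 1 and so have a shorter first-cycle exposure, count towards the DLT assessment.

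The cost is amendment wording and, if six patients are required, a short pause before full expansion while the additional patients are accrued and observed. No patients are added if the level passes, since they fall within the 27; up to three more are needed if it fails.
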